#### **4.3 Sample size calculation**

Aviophobia: An effect size of Cohen's  $d = 0.80$  was found from a meta-analysis of VR treatments for fear of flying (Fodor, 2018). Because ZeroPhobia: Aviophobia is a complete self-help treatment with rudimentary VR glasses, we have taken a slightly more conservative effect size of 0.70 as the starting point for the power calculation. To demonstrate a difference between the experimental and control condition with a standardized effect size of  $d = 0.70$  (tested on both sides), an alpha of 0.05 and a statistical power (1-beta) of 0.80, we have 34 respondents in each condition required (68 respondents in total). Taking into account a drop-out rate of 40% (Donker et al., 2019), we need a total of 96 respondents ( $n = 48$  per condition).

Arachnophobia: An effect size of Cohen's  $d = 1.11 / 1.12$  was found from a meta-analysis of VR treatments for different phobias, including fear of spiders (Opris et al., 2012,

Powers et al., 2008). Because ZeroPhobia: Arachnophobia is a complete self-help treatment with rudimentary VR glasses, we have taken a slightly more conservative effect size of 0.80 as the starting point for the power calculation. To demonstrate a difference between the experimental and control condition with a standardized effect size of  $d = 0.80$  (tested on both sides), an alpha of 0.05 and a statistical power (1-beta) of 0.80, we have 26 respondents in each condition required (52 respondents in total). Taking into account a dropout rate of 40% (Donker et al., 2019), we need a total of 72 respondents ( $n = 36$  per condition).

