- Professional treatment (medication and other psychiatric treatment) will be asked during the screening process, but also at post-test and follow up timepoints in order to control for possible other therapeutic effects.
- Negative Effects Questionnaire (NEQ; Rozental et al., 2016) consists of 32 questions and will be used to assess side effects of psychological treatments. Each question can be answered either ‘yes’ or ‘no.’ If yes, participants are then asked to rate how negative the experience of this item was on a 5-point Likert scale (from ‘not at all’ to ‘extremely’). Participants are then asked to determine whether this experience was probably caused by ‘the treatment that I am undergoing’ or ‘other circumstances.’ The NEQ has been found to have good validity (Rozental et al., 2019).

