## **10. STATISTICAL ANALYSIS**

### **10.1 Primary study parameter(s)**

The primary outcome measure (FAS for aviophobia, FSQ for arachnophobia) will be treated as a continuous outcome. Continuous variables will be presented as mean, standard deviation, and minimum and maximum number of observations. Descriptive statistics of demographics and clinical outcomes will be compared between the experimental and control condition. The quantitative analysis of the primary endpoints will be performed on an intention-to-treat basis following the per protocol analysis (PPA) according to CONSORT recommendations and SPIRIT guidelines for reporting results (Chan 2013a, 2013b; Eysenbach et al., 2011). Comparisons will be made between and within the groups for pre- and post-measurement and follow-up. Multiple imputation will be used in dealing with missing data, assuming this is "at random" (Brunton-Smith et al., 2014). We will calculate Clinical Meaningful Change on the FAS (Evans, 1998) and a reliable change criterion (Evans, 1998). We will also calculate the number needed to treat (NNT) based on (Christensen et al., 1986; Cohen, 1972). Standardized effect sizes (Cohen's d) and the confidence intervals are calculated. STATA version 16 will be used for the analyses. The best static analysis procedure to perform the analyses for this RCT will be reviewed before the data is analysed.

Intention-to-treat analysis will be used on continuous scales using repeated measures analysis of variance (ANOVA). Per protocol analysis will be performed by independent sample t-tests. Standardized effect sizes (Cohen's d) and confidence intervals will be calculated. SPSS version 21 will be used for the analyzes. A  $p$ -value  $<0.05$  will be considered to indicate statistical significance.

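### The primary analysis named in Protocol 10.1, a repeated-measures ANOVA, is less efficient than baseline-adjusted ANCOVA, and the same section leaves the method open

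*Protocol*

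**What the plan says.** Section 10.1 gives the primary method for FAS and FSQ: "Intention-to-treat analysis will be used on continuous scales using repeated measures analysis of variance (ANOVA". For the other analysis set it says: "Per protocol analysis will be performed by independent sample t-tests". Missing data are to be handled by multiple imputation under a missing-at-random assumption. The same section adds: "The best static analysis procedure to perform the analyses for this RCT will be reviewed before the data is analysed". Section 10 mentions neither ANCOVA nor baseline adjustment.

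Section 4.3 sizes each trial on a two-group standardised difference, "tested on both sides", with "an alpha of 0.05 and a statistical power (1-beta) of 0.80". The assumed effects are 0.70 (aviophobia) and 0.80 (arachnophobia). No correlation between baseline and post-test enters the calculation or appears anywhere else.

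Section 8.3 gives the 3- and 12-month questionnaires to the intervention arm only. Table 1 lists FAS or FSQ at baseline, post-test and follow-up. Section 8.1.3 says professional treatment is asked about at screening, "but also at post-test and follow up timepoints in order to control for possible other therapeutic effects"; Table 1 states a similar purpose.

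**The concern.** The randomised comparison has two time points. In that setting the group-by-time test of a repeated-measures ANOVA is exactly a t-test on change scores. That test gives the baseline a fixed coefficient of 1, whereas ANCOVA estimates the coefficient. The baseline score is therefore used less well than it could be, in two small trials that expect to lose 40% of participants. The planned test also differs from the post-test comparison on which the sample size rests.

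Two pieces of wording add to this. The primary method is both named and left open, in a trial that section 8.2 says cannot be double-blind. And the reason given for recording professional treatment after randomisation could be read as a plan to adjust for it. Section 11.3 lets participants seek other help, and being on a waitlist may affect whether they do. Adjusting for it could bias the randomised contrast.

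**Working it through.** **Inputs.** Section 4.3: d = 0.70 and 0.80, two-sided alpha 0.05, power 0.80, 34 and 26 evaluable per arm, 40% drop-out, 96 and 72 enrolled. Section 8.2: 1:1 allocation. Rho is not stated; 0.3 to 0.7 is assumed.

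**1. The plan's own figures.** A two-sample t-test (exact noncentral t) needs 34 per arm for d = 0.70 and 26 for d = 0.80, with power 0.81 in each case. Both reproduce.

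**2. Completers.** The enrolled totals follow from multiplying by 1.4: 68 × 1.4 = 95.2 and 52 × 1.4 = 72.8. Dividing by 0.6 gives 113.3 and 86.7, that is 114 and 87 (88 for equal arms). With 40% lost, 96 × 0.6 / 2 = 28.8 and 72 × 0.6 / 2 = 21.6 remain per arm. Post-test t-test power is then 0.74 and 0.73.

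**3. Three tests compared.** With equal SDs at baseline and post-test, set to 1, the variance of the arm contrast is proportional to:

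- post-test t-test: 1
- change score (group-by-time): 2(1 − rho)
- ANCOVA: 1 − rho²

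The ratio of ANCOVA to change-score variance is (1 − rho²) / [2(1 − rho)] = (1 + rho)/2, which is below 1 for every rho below 1.

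**4. Power at the completers of step 2.** Noncentral t with effective d of d/√(2(1 − rho)) for change and d/√(1 − rho²) for ANCOVA (one degree of freedom fewer). Example, aviophobia at rho 0.5: 0.70/√1 = 0.70 for change and 0.70/√0.75 = 0.808 for ANCOVA.

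| rho (assumed) | Aviophobia: change | Aviophobia: ANCOVA | Arachnophobia: change | Arachnophobia: ANCOVA |
|---|---|---|---|---|
| 0.3 | 0.597 | 0.781 | 0.583 | 0.767 |
| 0.5 | 0.742 | 0.854 | 0.728 | 0.842 |
| 0.7 | 0.921 | 0.955 | 0.912 | 0.949 |

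These treat completers as the information available. With only baseline and post-test in the imputation model, multiple imputation would add little to the post-test contrast.

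**5. Where 80% is reached.** ANCOVA crosses 0.80 at rho = 0.364 (aviophobia) and 0.402 (arachnophobia). The change-score test crosses it at 0.566 and 0.580.

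**6. Effect of the entry cut-off.** Sections 4.2 and 8.1.1 require a minimum FAS or FSQ score, which may shrink the baseline SD, and the equal-SD formulas then no longer apply. Assume a normal baseline with SD 1, a slope of post-test on baseline of 0.5, residual variance 0.75, and a cut removing half.

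- Baseline variance becomes 0.363.
- Post-test variance is 0.25 × 0.363 + 0.75 = 0.841.
- Change-score variance is (0.5 − 1)² × 0.363 + 0.75 = 0.841, the same.
- ANCOVA residual variance is 0.75, and 0.75/0.841 = 0.892.

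With d expressed in units of the restricted post-test SD, power is 74% for change and 79% for ANCOVA in aviophobia, and 73% and 78% in arachnophobia. The gain is about 5 points. Observed rho has fallen to 0.33, but the change-score test is no weaker than the post-test t-test.

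**7. Is the covariate kept?** Section 8.3 places FAS or FSQ in the screening survey, says all screening responses are deleted once eligibility is settled, and omits the scale from its baseline list. Section 11.2 limits deletion to ineligible people and includes FAS or FSQ at baseline, as does Table 1. The sections conflict.

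**The case against.** The case for leaving the plan alone is that repeated-measures ANOVA is valid and unbiased under randomisation, that t-tests in the per-protocol set are not an error, and that the size of any gain depends on a rho the protocol does not give. All of that stands. It makes this an improvement in efficiency, not the correction of an invalid test. Some stronger readings are tempting, and the document does not support them:

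- **That ANCOVA simply restores the power lost to drop-out.** At rho 0.3 it stays below 80% in both trials. At rho of about 0.58 or more, with equal SDs, the planned ANOVA reaches 80% without it.
- **That the entry cut-off lowers rho and so makes the planned test weaker than the one used for sizing.** Change beats or loses to post-test alone according to whether the slope exceeds 0.5, and truncating on baseline leaves the slope unchanged (step 6).
- **That the team may choose its test after seeing open-label results.** Section 10.1 places the review before analysis, section 12.1 merges the databases only after collection is complete and each is locked, and section 10.4 plans no interim analysis. The wording is loose because it does not say before outcome data are accessed, but it is no licence to choose on results.
- **That the ANOVA group main effect would be the test.** Nothing says so; section 10.1 speaks of comparisons between and within groups for pre- and post-measurement.
- **That the primary model will adjust for professional treatment.** Sections 8.1.3 and 8.3 (Table 1) state an intention to control for it, but no model in section 10 includes it.

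**Conclusion.** The point holds as one of efficiency and clarity. With two shared time points, the named primary test is a change-score test, and baseline-adjusted ANCOVA is more efficient for any rho below 1, using a score that Table 1 already schedules. With equal SDs and 40% drop-out, the gain is about 18 points at rho 0.3, 11 at rho 0.5, and 3 to 4 at rho 0.7. It is nearer 5 points if the entry cut-off shrinks the baseline SD as in step 6. All of these rest on an assumed rho or slope and on completers as the effective sample.

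ANCOVA gives 80% power at the planned numbers only if rho is at least roughly 0.37 (aviophobia) or 0.40 (arachnophobia). It does not replace correcting the drop-out inflation in section 4.3, and it does nothing about bias from missing outcomes, which rests on the missing-at-random assumption. The open-method sentence and the stated purpose for professional treatment are loose wording to tighten, not evidence of a biased analysis.

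**What to change.** 1. In section 10.1, name one primary analysis for each trial: ANCOVA of post-test FAS or FSQ on arm with baseline FAS or FSQ as covariate (or the equivalent baseline-adjusted mixed model), in all randomised participants with the planned multiple imputation.
2. Replace the sentence that leaves the procedure open with a statement that the method is fixed before outcome data are accessed.
3. Reconcile section 8.3 with section 11.2 and Table 1 so that a baseline FAS or FSQ is collected and retained for every randomised participant.
4. State that professional treatment reported after randomisation is described by arm and is not a covariate in the primary comparison.

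The cost is protocol wording. No extra participants or new measures are needed, provided item 3 is settled before baseline scores are lost. The drop-out inflation in section 4.3 needs its own correction.

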## **3. STUDY DESIGN**

A randomized controlled design will be carried out, in which the effectiveness and user-friendliness of an online app-based VR self-help treatment 'ZeroPhobia: Aviophobia' and 'ZeroPhobia: Arachnophobia' will be evaluated. In this study, 96 (aviophobia) and 72 (arachnophobia) participants from the Dutch general population will be randomized in 2 separate RCTs over 2 conditions: the experimental condition (ZeroPhobia: Aviophobia or Arachnophobia) and a waitlist control condition. The duration of the intervention will be 6 weeks. Measures will be taken at baseline, directly after the intervention (6 weeks) and at 3- and 12- month follow-ups. All measures will be completed online. Subjects in the wait-list condition will receive the intervention after completion of the post-test. Randomization (block randomization with 6, 8, 10, and 12 blocks) will be performed by an independent researcher. Figure 1 presents the flow chart of the study.

[figure not shown]

Figure 1: flow chart

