Ad 2) **Facing your fears**: In this module, the participant will define his/her goals for the treatment. Furthermore, the treatment principles underlying exposure are explained.

Ad 3) **Exposure in VR**: in this module, the VR content is explained and how to access it. Participants will practice in a practice-environment with VR before commencing the exposure therapy. After practice, the actual exposure takes place. In the VR environment, participants are exposed to situations involving flying/spiders. Participants can set the level of fear they would like to induce in the environment. Participants are informed that they can remove their VR glasses and exit the exposure at any time, especially if the fear induced is too challenging for them. After completing an exposure and based on his/her fear levels and performance, the user receives feedback. S/he can return to practicing in virtual reality as often as s/he likes and gradually expose him-/herself to different flight or spider situations and fear intensities. Only during the exposure sessions will the participant use the VR glasses.

Ad 4 and 5) **Cognitive therapy**: In these modules, according to the well-established principles of CBT, users identify and evaluate their catastrophic thoughts regarding their fear (e.g., “the airplane will crash” or “the spider will hurt me”).

Ad 6) **The Next Steps**: This module contains information on how the user can continue his/her practice and further reduce his/her fear and prevent relapse. This includes developing an individualized fear hierarchy. A fear hierarchy contains the necessary steps that need to be taken to reach one’s goals in the therapy. Explicit attention is devoted to motivation and encouragement.

The program further consists of:

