If in the intervention condition, the research assistant will send the VR glasses to the participant by postal delivery, along with usage instructions. The research assistant will email the participant with instructions on how to download the ZeroPhobia app to his/her smartphone. The app is locked with an individual code which will be given to the participant at the start of the intervention. Participants can then begin the ZeroPhobia intervention which they can follow for 6 weeks (5-20 minutes per week, in addition to VRET from module/week 3 onward, which we recommend 10 minutes a day of practice with). When practicing in VRET, participants are asked to fill in one question about their anxiety level before, during, and after VRET (duration: 5 seconds). Participants can follow the intervention at their own pace. Participants will receive weekly automatic reminder emails to begin or continue the intervention from the research assistant. If needed (e.g., with a question about how to use ZeroPhobia or in the unlikely case of distress), participants will be invited to contact the research assistant.

If in the wait-list condition, the participant will be informed that after a six week pause and the completion of a post-test assessment, they can begin the ZeroPhobia program. The wait-list group will undergo the same program procedure as those in the treatment condition. Participants of both conditions will begin the program on the first working Monday after

completing the baseline and being randomized to a condition, meaning participants of both groups will have different start and end times. Both groups will have the same duration of each section, however (see flowchart).

The aforementioned post-test (occurring after 6 weeks of either intervention or pause, or after the completion of module six in the intervention group (for those participants who choose to work through the ZeroPhobia program faster) consists of the FAS and FAM (aviophobia) or FSQ and SPQ, (arachnophobia), PHQ, BAI, IPQ, SUS, CEQ and NEQ, questions regarding whether they received professional treatment during this time, and questions about flight usage (duration: 25 minutes). Two reminders will be given across two weeks to fill in post-test, the first being an e-mail and the second a phone call.

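### Section 10.1 does not say whether ITT or per protocol decides effectiveness, and the per-protocol t-test can favour the app if its set depends on adherence

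*Protocol*

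**What the plan says.** Section 10.1 names two analyses of the primary endpoint. For the first: "Intention-to-treat analysis will be used on continuous scales using repeated measures analysis of variance (ANOVA"). For the second: "Per protocol analysis will be performed by independent sample t-tests". One threshold serves both: a p-value below 0.05 "will be considered to indicate statistical significance". On how the two relate, the section says only that the analysis of the primary endpoints "will be performed on an intention-to-treat basis following the per protocol analysis (PPA"). Sections 10.2 and 10.3 repeat that construction. No section defines the per-protocol set.

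On the control arm, section 3 says "Subjects in the wait-list condition will receive the intervention after completion of the post-test". Section 8.3 confirms that waitlist participants are told that "after a six week pause and the completion of a post-test assessment, they can begin the ZeroPhobia program". The app arm meanwhile has six modules, with daily VR practice recommended from module 3 onwards.

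Section 5.1 tells app users that they may leave an exposure at any time, "especially if the fear induced is too challenging for them". Section 8.6 keeps participants withdrawn from treatment in follow-up and puts all participants in the ITT analyses.

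**The concern.** Two features of the plan combine.

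The first is ranking. With two tests of one endpoint, one threshold and no clear order, a significant per-protocol result could be reported beside a non-significant ITT result, and section 10.1 would not settle which one answers the primary objective.

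The second is asymmetry. Up to post-test a waitlist participant can hardly fail to adhere, because there is nothing to adhere to except waiting and filling in a questionnaire. An app participant can stop. A set defined by adherence would therefore compare a selected part of one randomised arm with nearly all of the other. If those who persist would have scored better anyway, that difference is counted as treatment effect. An independent-samples t-test has no covariate with which to offset it.

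At stake is a claim of benefit that partly reflects who tolerated exposure rather than what exposure did.

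**Working it through.** **Inputs from the protocol.** There are 48 per arm (aviophobia) and 36 per arm (arachnophobia), allocated 1:1, tested two-sided at 0.05, with 40% drop-out expected (sections 4.3, 8.2 and 10.1). The 40% is an overall figure. It is not split by arm, nor into treatment stopping and missed assessment.

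**The plan's own figures.** The protocol gives no figure for the per-protocol analysis. Its completer numbers do reproduce: the exact two-sample t-test at 80% power needs 33.02 per arm for d = 0.70, rounded up to 34, and 25.52 for d = 0.80, rounded up to 26.

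**Assumptions, not in the protocol.**
- The app is inert: true difference 0, SD 1.
- A share s of the app arm stops and is removed from the per-protocol set. The waitlist is kept whole.
- rho is the correlation between the propensity to stop and post-test fear. It is positive if the more fearful stop.

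**Formula.** Spurious d = rho × φ(z) / (1 − s), where φ is the standard normal density and z the normal quantile at 1 − s. For s = 0.4, z = 0.253, φ(z) = 0.386, and 0.386 / 0.6 = 0.644. So:
- rho 0.2: 0.644 × 0.2 = 0.13
- rho 0.3: 0.644 × 0.3 = 0.19
- rho 0.4: 0.644 × 0.4 = 0.26

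**Simulation.** The app arm keeps 48 × 0.6 = 28.8, taken as 29, or 36 × 0.6 = 21.6, taken as 22. The t-test compares 29 v 48 or 22 v 36, with 8,000 to 40,000 simulated trials per case.

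| rho (40% stop) | Spurious d | Two-sided error, 29 v 48 | Two-sided error, 22 v 36 |
|---|---|---|---|
| −0.3 | −0.19 | 12.5% (0.3% favouring the app) | 10.5% (0.4% favouring the app) |
| 0 | 0 | 5% | 5% |
| 0.2 | 0.13 | 8% | 7% |
| 0.3 | 0.19 | 13% | 10 to 11% |
| 0.4 | 0.26 | 19 to 20% | 15% |

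For positive rho nearly all the excess favours the app. At rho 0.3 and 48 per arm, the error in its favour is 12.3% against a nominal 2.5%.

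**Sensitivity to the stopping share.** With 20% stopping, rho 0.3 and 38 v 48, the spurious d is 0.11 and the two-sided error 8.1%, of which 7.3% favours the app.

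**Two checks on the mechanism.** Analysing everyone randomised, with complete data, gives about 5% error in every case. Applying the same outcome-related exclusion to both arms (40%, rho 0.3) gives zero bias and errors of 5.2% (48 per arm) and 5.6% (36 per arm). The inflation therefore comes from the exclusion being one-sided.

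**The case against.** A reader might infer that the per-protocol test will show benefit even for an inert app. The documents do not support that. They give neither the app arm's stopping rate nor the link between stopping and outcome. The bias is zero if the two are unrelated. It reverses if participants who are less fearful or have improved early are the ones who stop, which is possible in a self-paced programme. Even under the assumptions above, an inert app gives no significant difference in most trials.

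The per-protocol set is also undefined. A statistical analysis plan that is not at hand may define it, and leaving the definition there is no fault. A set based on a completed post-test or on no outside treatment would exclude people from both arms. This stands: the asymmetry is a consequence of any adherence-based set, not something the protocol has already fixed. Exclusions of that other kind would not, however, mirror selection for tolerating exposure.

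A reader might also infer that per protocol may replace ITT. No sentence says so. ITT is planned, section 8.6 puts everyone in it, and reporting per protocol alongside it is ordinary practice. That limits the harm, but it does not supply the missing statement of which result decides.

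Finally, section 10.1 does not say whether the t-test uses post-test or change scores, and a change score would take some account of baseline. It also says the analysis procedure will be reviewed before the data are analysed. Neither point resolves the ranking.

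**Conclusion.** The point holds in a conditional form. Section 10.1 fixes a per-protocol t-test next to the ITT analysis under one significance criterion, and its wording on their order is unclear. The waitlist has no treatment to stop before post-test, so an adherence-based set would select within the app arm alone, and the t-test can then favour the app.

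With 40% stopping and rho 0.2 to 0.4, both assumed, the size is a spurious d of about 0.13 to 0.26. The two-sided error is about 8 to 20% at 48 per arm and 7 to 15% at 36 per arm. That the more fearful stop is plausible from the advice in section 5.1 on leaving an exposure, but it is not established. The planned ITT analysis does not carry this exclusion, so the trial's main comparison is not undermined. What needs repair is the ranking and the unadjusted supportive test.

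**What to change.** In section 10.1, state that the ITT analysis alone decides effectiveness and that the per-protocol result is supportive only. Reword the unclear phrase there and in sections 10.2 and 10.3.

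Replace the per-protocol t-test by a comparison of post-test scores adjusted for baseline FAS or FSQ, and say that this reduces but does not remove selection bias: it deals only with the part of stopping that baseline severity explains.

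A complier-average effect, with randomisation as instrument, may be added as an optional sensitivity analysis. Its assumptions need stating. Assignment alone must not affect a self-reported outcome in a trial without double blinding, and participants counted as unexposed must gain nothing. The second is doubtful if exposure is counted from module 3, because modules 1 and 2 already deliver content. Its interval would also be wider.

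The cost is a few sentences and one covariate. Table 1 and section 11.2 list FAS or FSQ at baseline. Section 8.3 omits it from the baseline survey and says all screening responses are deleted, so those passages should be reconciled to ensure the baseline score is kept.
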